**Methods:**

This will be a parallel-group randomized controlled trial of 4-week Breaking Free Online Health and Justice program as an adjunct to standard treatment for substance misuse, in comparison to standard treatment only, in a male Category D open prison. Interventional and control groups will be compared in terms of the changes in their scores on multiple measures from baseline to post-treatment assessment at 4-weeks, and then 3- and 6-months follow-up. Participants will be adult male offenders serving sentences in prison in England who have demonstrable difficulties with drugs and/or alcohol for at least the past 12-months. The primary outcome measure will be self-reported substance misuse, with secondary outcomes being standardized psychometric assessments of substance dependence, mental health, biopsychosocial functioning, quality of life and post-release offending. Other secondary measures will include frequency of completion of specific intervention strategies in the program.

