### Setting

The study will be conducted in an adult male prison in North-West England, UK, where the BFO program is not currently delivered as a standard treatment. This prison is a ‘Category D’ open prison where offenders are, subject to approval, provided with ‘Release on Temporary License’ (ROTL) where they are granted release to work in the community or have ‘home leave’. This prison is a resettlement prison which has an operational capacity of just over 600 male offenders, approximately a quarter of whom are either on life sentences or subject to indeterminate sentences. Approximately, 75% of the men in the prison are serving sentences of 4-years or longer at any one time. Around three-quarters of the men in the prison are over the age of 30 years, and around 40% have identified substance misuse difficulties. The prison places a strong emphasis on rehabilitation and community reintegration, running a range of vocational training courses, alongside initiatives to support the men serving sentences in the prison to maintain and enhance the relationships they have with their families.

This category of prison has been chosen for the study because, although even the very highest security prisons in the UK have significant issues with drug and alcohol use, offenders in a Category D prison may potentially have the most opportunity to use substances, as they spend some of their time in the community. Most participants may be on ROTL during the study, including resettlement day release, and resettlement overnight release, so it is more likely that outcomes related to substance use will be an artifact of treatment effects, rather than lack of opportunity to use substances due to incarceration in a highly secure environment. Although it is anticipated that most, if not all, participants will be receiving ROTL during the study, the ROTL status of each participant will be recorded during their first treatment session and this will be taken into account during data analyses, if there are a significant number of participants not provided with ROTL during the study. Participants will be recruited from standard alcohol and drug misuse services in the prison, which are delivered in coordination with Her Majesty’s Prison and Probation Service (HMPPS).

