
In addition to the standardized measures described above, socio-demographic data will also be collected via the digital assessment completed by both study groups, including age and ethnicity. Additional socio-demographic data will be collected via paper/pen assessment when participants are first randomized, including educational level achieved, employment status before entering prison, and marital status (See Additional file 1: Appendix A), and what standard treatments each participant has received (see Additional file 1: Appendix B). This will allow comparisons of the two study groups to be made, and also comparisons of all participants with data published each year by the UK Ministry of Justice describing the broader prison population in England and Wales.

When follow-up assessments are conducted at 3- and 6-months, each participant will also be asked about any further involvement with criminal justice authorities since being released from prison, if they have been released from prison in the interim, and if so, the nature of this involvement with the authorities, e.g. being arrested, any court appearances etc. (See Additional file 1: Appendix C). For ethical and legal reasons, these questions will be restricted to questions that enquire as to criminal justice system involvement only, as opposed to asking participants about any crimes they may have committed that may not have been discovered by the authorities.

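### Post-release offending is asked about only in men already released at the visit and only since release, so it cannot be compared cleanly across all randomized men

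*Protocol article*

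**What the plan says.** The Methods part of the abstract lists among the secondary outcomes "biopsychosocial functioning, quality of life and post-release offending". The same paragraph says: "Interventional and control groups will be compared in terms of the changes in their scores on multiple measures", with assessments at 4 weeks, 3 months and 6 months.

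Measures gives the collection rule. At 3 and 6 months each participant is asked about "any further involvement with criminal justice authorities since being released from prison", and this only "if they have been released from prison in the interim". For ethical and legal reasons the questions are "restricted to questions that enquire as to criminal justice system involvement only", such as arrests or court appearances. The form itself is Appendix C of the supplementary file, which is not shown.

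Four other places bear on this rule:

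- **Participants** requires at least 3 months left to serve at the research site at recruitment, and sets no upper limit.
- **Setting** puts about 75% of the prison on sentences of 4 years or longer, with "approximately a quarter of whom are either on life sentences or subject to indeterminate sentences". It also expects most participants to be on temporary release (ROTL) during the study.
- **Procedure** has every participant followed up. Men still in custody, transferred or reconvicted are visited in prison.
- **Data analysis** promises an intention-to-treat analysis of all randomized men. The five outcomes it names for the between-group model do not include offending.

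**The concern.** Whether a man supplies any offending data depends on an event after randomization, his release. How much data he supplies depends on when that event occurs. Two analyses are then open, and neither is clean:

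- **Released men only.** The groups compared are formed after allocation, so randomization does not guarantee that they are alike.
- **All randomized men, with unreleased men counted as event-free.** The result depends on how many men were released and how early, as well as on what they did afterwards. A man kept in custody counts as a success.

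There is also a gap before release. The protocol chose an open prison because its men spend time in the community, and it relies on that time to justify the primary outcome. An arrest during temporary release appears not to be asked about.

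The Background says the programme is designed to address substance misuse and offending together, and this is the only offending measure described. An analysis plan can choose a model or adjust for exposure if release dates are held. It cannot supply answers to questions that were not put.

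**Working it through.** **Inputs from the protocol**

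- Randomization to baseline: 0 to 2 weeks (Procedure).
- Treatment: 4 weeks (Design, Procedure).
- Follow-up: 3 and 6 months after treatment (Procedure).
- Earliest end of sentence: 3 months after recruitment (Participants).

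**Working assumptions.** Recruitment and randomization are taken as the same date, visits as on schedule, and no man as released before his 3 months are served. With 52.18 weeks to the year, 4 weeks = 4 × 12/52.18 = 0.92 months and 2 weeks = 0.46 months.

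**Step 1: the protocol's own figure.** From baseline to the last visit is 0.92 + 6 = 6.92 months. This agrees with the total of approximately 7 months given in Procedure.

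**Step 2: visit times after randomization**

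- 3-month visit: (0 to 0.46) + 0.92 + 3 = 3.92 to 4.38 months.
- 6-month visit: (0 to 0.46) + 0.92 + 6 = 6.92 to 7.38 months.

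**Step 3: longest possible time at risk.** This is the visit time minus 3 months.

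- 3-month visit: 0.92 to 1.38 months.
- 6-month visit: 3.92 to 4.38 months.

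The shortest is 0 at both visits, because there is no upper limit on time left to serve.

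**Step 4: what unequal exposure does to a crude proportion.** Assume, for illustration only, a constant hazard of 0.05 per month, so that P(event) = 1 − exp(−0.05 × months).

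- 0.5 month at risk: 2.5%.
- 4.4 months at risk: 19.7%.

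Two men with identical behaviour thus differ about eightfold (19.7/2.5 = 7.9) through release date alone.

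**Step 5: how many men would contribute.** The protocol gives no release rate. If 10% to 75% of men are released by the visit (assumption), the numbers per arm are:

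- 120 men followed: 60 × 0.10 = 6 to 60 × 0.75 = 45.
- 60 men followed: 30 × 0.10 = 3 to 30 × 0.75 = 22–23.

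Both totals are shown because Power calculation can be read as leaving 60 per arm after the 50% attrition, or as losing half of those 60.

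**Step 6: the temporary-release gap.** Procedure sets men released back to the community against men still serving their sentence, so release there means final release. Read the same way in Measures, the window opens only at final release and earlier time on ROTL lies outside it.

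**The case against.** The strongest reply is that the outcome is post-release offending, which by definition requires release. A man not released has had no post-release event, and Procedure establishes release status for everyone. The analysis plan could therefore define any post-release involvement by 6 months over all randomized men. This stands: a reader might infer that no all-randomized comparison is possible, and that would be wrong. But such an outcome combines being released with reoffending, and the collected data could not separate a lower offending rate from later release unless release dates are also recorded.

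Other stronger readings are not supported either:

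- **That the plan fixes a released-only test between arms.** Data analysis does not list offending in its model, and Power calculation speaks of descriptive comparisons. A comparison is implied by the abstract, but its form is left open, and an exposure-adjusted analysis in the unseen plan cannot be ruled out.
- **That time at risk differs between the arms.** It is shown to differ between men. Variation common to both arms adds noise but does not by itself cause bias. Time left to serve is checked at recruitment, so randomization balances it in expectation. If release dates were fixed at that point and unaffected by allocation, the released men would be comparable in expectation. The documents do not say that they are fixed, and a quarter of the prison has life or indeterminate sentences.
- **That release depends on progress in treatment.** This is plausible but not stated.
- **That contact during temporary release is certainly missed.** Setting itself calls ROTL a form of release, and Appendix C may ask more than the article's one sentence.
- **That the comparison has some particular low power.** Release and event rates are not given, and low power for a secondary outcome would not show the collection rule to be faulty.

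Finally, asking only about the time after release is a legitimate choice of question. That is a reason to keep post-release involvement as a reported outcome alongside a broader one.

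**Conclusion.** The point holds as a defect in data collection for one secondary outcome. The rule in Measures leaves either a comparison among released men, which randomization does not protect, or one in which continued custody counts as success. Time at risk runs from 0 to about 0.9–1.4 months at the first follow-up and from 0 to about 3.9–4.4 months at the second. These ranges follow from the protocol's schedule and the assumptions stated with the calculation. The hazard and release shares are illustrations only.

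The temporary-release gap is likely from the way Procedure uses the word released, but is not certain without Appendix C. Bias between arms is not shown. The primary outcome and the five modelled outcomes are unaffected. The change is worth making before data are collected, because the missing answers could not be reconstructed reliably afterwards.

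**What to change.** 1. At 3 and 6 months, ask every participant about criminal justice involvement (arrest, charge, court appearance, recall to prison) since the last assessment, whether he is in custody, on ROTL or released. Let the first of these questions reach back to randomization, so that the treatment period is covered.
2. Record the date of release for every man.
3. Compare any involvement by 6 months across all randomized men.
4. Report post-release involvement per month in the community among released men, labelled as descriptive and non-randomized.
5. If Appendix C already covers temporary release or men in custody, correct the sentence in Measures to say so.

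The cost is a reworded item and one date on a form used at visits that already take place. Procedure already has staff establish who has been released and visit those in custody. The questions stay within the protocol's limit to contact with the authorities. The downsides are a slightly longer form and a broader outcome reported beside post-release offending. The change does not help with men lost to follow-up, whose missing answers still have to be handled in the analysis.

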### Data analysis

Quantitative data will be analyzed and reported using SPSS® Version 25.0 (or later) with all analyses to be performed as per the statistical analysis plan. The appropriate 95% - confidence interval will be applied. The *all-randomized population* will consist of all participants in the study that have been screened and allocated to either the i) BFO plus standard treatment, or, ii) standard treatment only group. The *per-protocol population* will consist of all participants randomized into the study who have completed the 4-week treatment period as well as all follow-up assessments.

Analyses will be performed on the basis of an ITT population, with the all-randomized population included in the analyses. No participants will be excluded from the ITT analyses, i.e. those who have withdrawn, been lost to follow-up, or have provided incomplete outcomes data. Separate analyses will also be conducted on the per-protocol population who have provided at least one set of follow-up data. Outcomes from these two analyses (ITT, per-protocol population) will be compared to examine whether missing data may have had an impact on reliability of conclusions formed around comparative effectiveness of the two study conditions.

Previous analyses (e.g. Elison et al. 2015a, b, c) indicate that data will likely be non-normally distributed in which case nonparametric repeated-measures analyses of covariance (ANCOVA) using appropriate distribution such as Poisson distribution, will be used to compare the study groups at 4-weeks post-treatment and 3- and 6-months follow-up on self-reported substance use, substance dependence, mental health sequelae, biopsychosocial functioning and quality of life. However, normality will be tested when data are available for analyses, and appropriate distributions will be applied.

Specialist statistical support has been sought from colleagues at one of the collaborating academic institutions (University of Manchester), who have provided advice during protocol development and will provide ongoing advice throughout the study. When analyzing differences between the two study groups at each of the outcomes data time-points, (4-weeks post-treatment, 3- and 6-month follow-ups) baseline scores will be controlled for as post-treatment between-group differences may reflect both treatment effects and also group differences at baseline that randomization may not have addressed. Differences between the groups in post-treatment scores will be ascertained using estimated marginal means.

Effect sizes will also be calculated to examine robustness of between-group differences and within-group changes over time, using partial eta squared (ὴ^2^), which is an appropriate measure of effect size for ANCOVA. The numbers of participants fulfilling clinical threshold scores for substance dependence, depression and anxiety at baseline and post-treatment will also be examined.

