### Power calculation

Since the study is a parallel-group comparison, equal numbers of participants will be required for each of the groups; i) BFO plus standard treatment, and, ii) standard treatment only. The study projection of the sample size will require 60 evaluable participants in each treatment group to achieve enough power (assuming power of 0.80 with α = .05) with an allowance of 50% attrition at 3- and 6-months follow-up, which is in line with previous studies with offender populations receiving interventions for substance misuse in correctional settings (e.g. Crisanti et al. 2014). In addition, this level of attrition is also seen in substance misuse intervention research more generally (e.g. Brorson et al. 2013) and in many digital interventions studies (e.g. Eysenbach 2005). To obtain a total of 120 evaluable participants, it is estimated 240 participants will need to be recruited and screened.

These estimations have been based on previous samples used for assessments of CAT (Carroll et al. 2008), some of which have used longitudinal statistical analyses (Koski-Jännes et al. 2009; Kypri et al. 2008). It is envisaged that the estimated evaluable participant population will be sufficiently large to enable meaningful descriptive comparisons to be performed.

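### The analysis plan calls a Poisson model nonparametric, lets a normality test on trial data choose the primary model, and pairs it with an effect size that does not fit a Poisson model

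*Protocol article*

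**What the plan says.** The Data analysis section of the protocol article expects non-normal data and in that case plans "nonparametric repeated-measures analyses of covariance (ANCOVA) using appropriate distribution such as Poisson distribution". One sentence applies this to self-reported substance use (primary), dependence, mental health, biopsychosocial functioning and quality of life, at 4 weeks and at the 3- and 6-month follow-ups. It then adds that "normality will be tested when data are available for analyses, and appropriate distributions will be applied". The section opens by referring to a statistical analysis plan, which is not shown.

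Baseline scores are to be controlled for, and group differences are to be obtained from estimated marginal means. On effect measures it states: "Effect sizes will also be calculated to examine robustness of between-group differences and within-group changes over time, using partial eta squared".

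The Measures section builds the primary outcome from an amount per typical day, in a unit that depends on the substance, and the number of days of use in a typical week. The secondary scales are sums of bounded ratings: SDS (5 items, 4 points), PHQ-4 (4 items, 4 points), five WHOQoL-BREF items (5 points), and the RPM (six 11-point sliders plus 30 yes/no items).

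**The concern.** Four things in this text do not fit together.

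- A model with a Poisson distribution is parametric. Calling it nonparametric leaves the reader unsure which method is meant.
- The only distribution named is one for event counts. It is offered for an amount multiplied by days and for bounded rating sums, and neither is a Poisson count.
- The primary model is to be settled by a normality test on the trial's own outcome data. Rejecting normality does not make Poisson suitable, because what matters for Poisson inference is whether the variance equals the mean.
- Partial eta squared is defined from sums of squares in a linear model. It has no sign and says nothing about robustness.

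At stake is the validity of the primary p-value if the plan is carried out in its plainest form, and the credibility of a primary model chosen after the outcome data are in hand.

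**Working it through.** **Inputs from the protocol article.** Power and alpha: "assuming power of 0.80 with α = .05" (two-sided assumed). Sample: "60 evaluable participants in each treatment group", with "an allowance of 50% attrition at 3- and 6-months follow-up", which leaves 30 per group if taken from 60. No mean, zero share, variance or dispersion is given for substance use.

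**1. The plan's own figure.** 120 / (1 − 0.5) = 240, so the recruitment target reproduces. The 60 per group does not, because no effect size or SD is stated. It corresponds to a standardised difference of (1.96 + 0.84) × √(2/60) ≈ 0.51. Nothing in the power section informs the choice of distribution.

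**2. Size of a model-based Poisson test.** Let φ = variance / mean after adjustment. The model-based standard error is too small by √φ, so the true two-sided size at nominal 5% is 2 × [1 − Φ(1.96/√φ)].

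| φ (assumed) | 1.96/√φ | true size |
|---|---|---|
| 0.5 | 2.77 | 0.6% |
| 1 | 1.96 | 5% |
| 1.5 | 1.60 | 11% |
| 2 | 1.39 | 17% |
| 5 | 0.88 | 38% |
| 10 | 0.62 | 54% |
| 20 | 0.44 | 66% |

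**3. Dependence on the recording unit.** Multiply every use value by a constant k (a finer unit). With a log link the treatment coefficient is unchanged, because log k goes into the intercept. The Poisson information is multiplied by k, so the model-based standard error is divided by √k. With k = 10, z = 1.0 (p = 0.32) becomes z = √10 = 3.16 (p = 0.002) on the same data. A sandwich standard error does not change: its inner term grows by k² and each outer term shrinks by k. This concerns one common change of unit. How amounts of different substances are combined is a separate matter.

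**4. Simulation with no treatment effect.** One time point, log-link Poisson adjusted for baseline, 60 per group, 1,500 runs per scenario. All distributions and item scorings are assumptions. Entries are rejection rates at nominal 5%.

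| Outcome type | residual φ | model-based | sandwich | scaled (quasi-Poisson) |
|---|---|---|---|---|
| True Poisson | 1.0 | 6% | 6% | 6% |
| Use, 55% zeros, mean 2 | 3.8 | 36% | 6% | 7% |
| Use, 31–71% zeros, mean 10–14 | 17–62 | 67–82% | 6–8% | 8% |
| SDS-like, PHQ-4-like | 1.5–2.5 | 10–20% | 5–6% | 4–5% |
| RPM-slider-like | 4.0 | 31% | 5% | 4% |
| WHOQoL five-item-like | 0.72 | 2% | 6% | 5% |

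Simulation error is about ±1 point near 5% and ±2.5 points near 50%. With 30 per group the model-based rates barely change (2–82% across the non-Poisson scenarios), and the sandwich rates are about 6–10%.

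A separate simulation with different assumed use data gave 25% (φ about 3) and 67% (φ about 19) model-based, against about 6% with an HC3 variance. These agree with the formula in step 2.

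**5. A repeated-measures version.** Exchangeable Poisson GEE with robust standard errors, three visits, baseline-adjusted, assumed dispersion about 20, 400 runs: 5.3% rejection at 60 per group and 8% at 30. The single-visit model with model-based errors rejected 70% on the same data.

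**6. Effect measure.** Partial eta squared = SS(effect) / [SS(effect) + SS(error)]. A Poisson model is fitted by likelihood and has no error sum of squares, so the quantity is not defined for it. Where it is defined it lies between 0 and 1, so it cannot show which group did better.

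**The case against.** The strongest reply is that the protocol does not commit to Poisson. It is introduced as an example, the closing sentence speaks of distributions in the plural, and the details are referred to a statistical analysis plan. The protocol also specifies a repeated-measures analysis, which for count-type data would normally mean GEE or a mixed model. With robust errors, step 5 shows rejection close to nominal at 60 per group. All of this stands.

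A reader might therefore infer from the large percentages that false positives will be common in this trial. The documents do not support that. It needs model-based standard errors, which the protocol nowhere specifies, and overdispersion, which it nowhere reports. The floor effect raised in the Discussion concerns biopsychosocial functioning, not substance use. The result is also sensitive to the assumption: days per week is bounded at 7, and with strong within-person consistency assumed, the model-based test rejected only about 1%. Nor can one say that scale scores would inflate error generally, since the WHOQoL-type score is conservative.

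A reader might also infer that the distribution will be picked with allocation visible. The Discussion says investigators and practitioners cannot readily be blinded, but nothing says the normality check uses group labels.

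Finally, partial eta squared is legitimate if a normal-theory ANCOVA is used, and the protocol already plans estimated marginal means and 95% confidence intervals.

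What the reply does not remove is the stated text: the contradictory label, the after-the-fact selection rule that tests the wrong assumption, and an effect size that does not fit the only non-normal distribution named. These are not details left to an analysis plan. An analysis plan that fixed the model in advance would depart from the rule published here.

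**Conclusion.** The concern holds in conditional form. The protocol states a self-contradictory method, lets a normality test on outcome data choose the primary model without checking the Poisson mean–variance assumption, and names an effect measure that does not fit a Poisson model and does not measure robustness. These faults rest on the text alone.

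The consequence for type I error is conditional. If a Poisson model with model-based standard errors were used on overdispersed use data, size could be well above 5%: about 17% at dispersion 2 and 38% at dispersion 5, both dispersions being assumed. In that same case the p-value would depend on the unit of recording. For scale scores the error could go in either direction. With sandwich or scaled errors the assumed scenarios come back to about 4–8% at 60 per group. No figure here is a prediction for this trial.

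**What to change.** In the Data analysis section, and in the analysis plan to match:

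- Delete the word nonparametric, and delete the normality test as the means of choosing the model. Residuals can still be examined and reported.
- Before any outcome data are seen, fix one model per outcome type. For substance use: a baseline-adjusted repeated-measures model with a log link and robust (sandwich) variance, or negative binomial. The log link with robust variance has the advantage that its p-value does not depend on the recording unit. For the scale scores: a linear mixed ANCOVA with robust standard errors.
- Because sandwich rejection rates reached 6–10% at 30 per group, state whether a small-sample correction will be used at the follow-up visits.
- Prespecify one alternative model as a sensitivity analysis.
- Replace partial eta squared with the ratio of means (use) or the adjusted mean difference (scales), each with its 95% confidence interval.

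The cost is minor rewording and somewhat wider intervals than model-based Poisson errors would give on overdispersed data. No additional data or participants are needed.
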